### 2.6. Patient and Public Involvement Statement

This study is a retrospective study based on past medical records, and there is no involvement of patients or the general public.

## 3. Discussion

We established a method for extracting real-world outcomes of systemic cancer therapy and its background factors using the Tokushukai medical database. Following the main protocol, we will plan sub-projects that allow us to examine the treatment outcomes of each cancer type. Our real-world evidence could complement the findings of traditional RCTs and provide valuable information for future research directions, policy initiatives, medical guidelines, and clinical decision-making. The research results will be published in peer-reviewed journals and presented at both national and international scientific conferences, as well as patient organizations.

### Strengths and Weaknesses

This nationwide cohort study will include a large number of patients from community-based general hospitals only, not including cancer centers or academic institutions. The cohort will comprise a certain number of patients who are unable to participate in clinical trials owing to their age, poor performance status, or complications. Therefore, this study could provide more realistic clinical data with a lower rate of loss to follow-up.

Moreover, our study will simultaneously use demographic data and treatment details, as well as the National Cancer Registry, DPC, prescription, and laboratory test data. In particular, few large-scale databases include performance status and laboratory data, which would be major considerations regarding prognostic factors. In addition, by using the DPC data, detailed information on emergency hospitalization, length of hospital stay, concomitant complications, medical costs, and outcomes can be obtained, allowing for a review of the quality and cost-effectiveness of medical care. Prescription data would be useful for evaluating drug–drug interactions. Relative dose intensity can also be computed. Individual analyses using institutional or national databases are very common; however, to the best of the authors’ knowledge, this is the first large-scale cohort study that can simultaneously handle comprehensive RWD.

In this study, it will be difficult to extract data without using a unified description format or sentences as descriptions in ordinary medical records. For instance, the time to treatment failure is easy to obtain, although there is no distinction between refractory and intolerant. Progression-free survival and recurrence-free survival can only be obtained through direct checks of medical records, although they are less reliable in retrospective studies [25]. In the same context, direct access to medical records is mostly required to obtain information on genetic mutations [26], which becomes an essential step when conducting standard treatment for many cancer types because the Japanese National Cancer Registry does not contain it, and most results of genetic alteration tests are included as images after outsourcing to testing companies. With regard to adverse events, laboratory data can be easily extracted and evaluated; however, it is difficult to handle imaging findings, such as intestinal lung disease, or subjective symptoms, such as nausea and vomiting. The electronic medical record system is equipped with software that evaluates and inputs according to CTCAE, but it is not sufficiently widespread during the current study period. Similarly, there is no provision for the patients’ quality of life scores to be routinely entered in the electronic medical record; thus, it is impossible to extract such data from our medical records, although its usefulness has been established [27]. These limitations indicate if there is good or poor compatibility among sub-projects for each type of cancer and treatment.

## 4. Ethics and Dissemination

All procedures performed in this study will be in compliance with the “World Medical Association Declaration of Helsinki” (revised in October 2013) and “Ethical Guidelines for Medical Research for Humans” (2014 Ministry of Education, Culture, Sports, Science and Technology, Ministry of Health, Labor and Welfare Notification, revised in February 2017).

Because this study will be carried out using existing information held by one’s own research institution, it is not always necessary to receive informed consent from the patients; however, information about the study, including the purpose of use of the information, will be notified or disclosed to the patients. Therefore, documents approved by the Joint Ethics Review Committee will be posted on the website of the Tokushukai Medical Group. We will publicly announce the research content and accept any requests for refusal to use the personal data. The patient will never be penalized if they decide to refuse participation.

When processing information associated with the conduct of the research, a number unrelated to the individual’s personal information (research subject identification code) is assigned in advance and managed as anonymization, and sufficient consideration is given to the protection of the research subject’s confidentiality. The correspondence table is strictly stored by the electronic medical record manager (Tokushukai Information System Inc.) and personal information manager. This number is used when sending information to the Department of Medical Oncology and Hematology, Kobe University Hospital, and deCult Co., Ltd. and gives due consideration to ensure that the personal information regarding the research subjects will not be disclosed outside the hospital. In addition, when the principal investigator publishes the information obtained in this study, care will be taken not to include information that can identify the research subjects.

## Figures and Tables

**Figure 1 healthcare-10-02146-f001:**
[figure not shown]
Data collection overview.

**Table 1 healthcare-10-02146-t001:** Inclusion and exclusion criteria.

Inclusion Criteria
Patients with pathologically or radiologically diagnosed cancer Age ≥20 years Receiving centrally registered systemic therapy at DPC hospitals within the Tokushukai Medical Group from 1 April 2010 to 31 March 2020
Exclusion criteria
Patients who chose to opt out Simultaneous and metachronous double cancer with disease-free interval of ≤5 years, except for carcinoma in situ/intramucosal cancer cured by local treatment or endoscopic lesions diagnosed as carcinoma in situ Inadequate data extraction (e.g., missing details on past cancer treatment at other hospitals or individual patient data)

**Table 2 healthcare-10-02146-t002:** Laboratory test information.

Blood cell counts	White blood cell (WBC), red blood cell (RBC), hemoglobin (Hb), platelet (PLT), leukocyte fraction, lymphocyte (Lym), neutrophil (Neu), monocyte (Mono), eosinophil (Eo), and basophil (Baso)
Biochemical tests	Sodium (Na), potassium (K), chloride (Cl), calcium (Ca), inorganic phosphorus (IP), magnesium (Mg), aspartate aminotransferase (AST), alanine aminotransferase (ALT), lactate dehydrogenase (LDH), alkaline phosphatase (ALP), γ-glutamyl transpeptidase (GGT), total bilirubin (T-Bil), direct bilirubin (D-Bil), blood urea nitrogen (BUN), creatinine (CRE), uric acid (UA), total protein (TP), albumin (Alb), blood glucose (Glu), hemoglobin A1c (HbA1c), total cholesterol (TC), HDL cholesterol, triglyceride (TG), C-reactive protein (CRP), iron (Fe), and ferritin
Tumor markers	Squamous cell carcinoma-related antigen (SCC), cytokeratin 19 fragment (SYFRA), carcinoembryonic antigen (CEA), carbohydrate antigen 19-9 (CA19-9), carbohydrate antigen 15-3 (CA15-3), carbohydrate antigen 125 (CA125), neuron-specific enolase (NSE), pro-gastrin-releasing peptide (ProGRP), and prostate specific antigen (PSA)
Coagulation/fibrinogenic tests	Activated partial thromboplastin time (APTT), prothrombin time (PT), fibrinogen (Fib), fibrin/fibrinogen degradation product (FDP), and D-dimer
Infectious disease markers	Hepatitis B surface (HBs) antigen, HBs antibody, HB core antibody, HBe antigen, HBe antibody, HB virus DNA quantification, HC virus antibody, syphilis, and HIV
Urinalysis parameters	Urine protein qualitative, urine sugar qualitative

**Table 3 healthcare-10-02146-t003:** Sample size of each cancer type.

Biliary tract cancer	800
Breast cancer	10,000
Colorectal cancer	10,000
Esophageal cancer	1000
Gastric cancer	5000
Gastrointestinal stromal tumor	500
Kidney cancer	350
Liver cancer	500
Lung cancer	10,000
Ovarian cancer	1500
Prostate cancer	5000
Pancreatic cancer	2500
Uterine body cancer	350
Uterine cervix cancer	350
Urothelial cancer	1000

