The Tokushukai Medical Group is a leading medical group in Japan that includes 71 general hospitals nationwide from Hokkaido to Okinawa, with a total of 18,000 beds, accounting for approximately 1.2% of all hospital beds in Japan [17]. The electronic medical record system that we use is unified, and medical coding of medication names and laboratory test values is standardized. This medical record system is managed by Tokushukai Information System Inc., and the patients’ medical information can be extracted from each hospital’s patient registration system. For systemic cancer therapy, a shared chemotherapy protocol system was installed in 51 hospitals by the end of March 2020. All prescribed chemotherapy regimens are approved by the regimen review committee of the Tokushukai Medical Group; therefore, the treatment schedule and dosage are unified nationwide. Among these hospitals, 46 hospitals applied the diagnosis procedure combination data (DPC), which is the Japanese claims record for acutely hospitalized patients, including information on the main diagnosis, interventions, and comorbidities. The DPC was developed as a measurement tool aimed at making acute hospital care transparent, standardizing Japanese medical care, and evaluating and improving its quality [18].

The Tokushukai REAl-world Data (TREAD) project is being developed as an observational population-based retrospective cohort study that aims to collect RWD on systemic therapy for Japanese patients with cancer in the Tokushukai Medical Group with this merit of scale.

Here, we report the main protocol of the study that will generate data through several sub-projects for each type of cancer to assess whether the results of clinical trials extend to the real world. Moreover, the data will enable the examination of temporal trends in treatment patterns, as well as treatment outcomes and prognostic factors that affect overall survival. 

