### 2.2. Information Source and Data Collection

Information on the patients who met the inclusion criteria will be extracted by the Tokushukai Information System Inc., while researchers will be blinded to statistical analyses. Figure 1 provides an overview of how variables will be collected.

Patient demographic data, including age, birth year and month, sex, postal code, and insurance type, were documented at the time of the issuance of medical record identification. In addition, body height, body weight, body mass index, body surface area, and date of measurement were recorded based on practical requirements. Moreover, the date of the last visit, the last date of survival confirmation, the date of death, and the diagnosis on medical receipt were automatically recorded as part of routine clinical practice. The above information can be extracted from a unified medical record system (e-Karte and Newtons2, Software Service, Inc., Osaka, Japan).

Treatment information, including inpatient and outpatient therapies, particularly chemotherapy regimens, can be retrieved from a shared chemotherapy protocol system (SSI srvApmDrop, Software Service, Inc., Tokyo, Japan). This system links the start and end date, the date of administration, the treatment interval, the number of treatment cycles, the dose of administration, the data of dose adjustment, and the performance status.

Data from the Japanese National Cancer Registry [19,20] are available for all hospitals, including the diagnosis (date, site, laterality, pathology, and differentiation), staging (clinical and pathological TNM classification [21]), date of the first visit, treatment details (surgery, endoscopic treatment, radiotherapy, chemotherapy, and endocrine therapy), and survival outcomes (last date of survival confirmation, date of death, and cause of death).

Patient, treatment, and cancer registry data are combined with anonymized identification and cleaned by Tokushukai Information System Inc. (Osaka, Japan). Patients with double cancer and/or diagnostic errors will be excluded from the study. Treatment history will be organized, and missing data will be supplemented by a direct check of medical records in cases of inconsistency or lack of information. Patients with unknown treatment history will be also excluded.

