Details of hospitalization information such as diagnosis at admission (ICD-10), type of admission (scheduled or emergency), date of admission and discharge, outcome at discharge, complication (ICD-10), costs, and history of smoking (Brinkman index) can be extracted from the DPC data, which serves as the National Hospital Discharge Database for clinical studies in Japan [18,22].

Prescription data, such as the name and dose of the medicine, as well as the date and days of prescription, can be added from the electronic ordering system (e-Karte and Newtons2). The following treatment agents will be assessed in this study: (1) antitumor agents, (2) antihypertensive agents, (3) antithrombotic and antiplatelet agents, (4) antidiabetic agents, (5) antilipidemic agents, (6) antibacterial/antiviral/antifungal agents, (7) antiacid agents, (8) steroids, and (9) probiotics.

Furthermore, laboratory test information, such as blood cell count, biochemical tests, tumor markers, coagulation/fibrinogenic tests, infectious diseases, and urinalysis, can be retrieved from the electronic ordering system (e-Karte and Newtons2). The detailed parameters are listed in Table 2. Admission, prescription, and laboratory test data are combined with basic patient information with anonymized identification and cleaned again by Tokushukai Information System Inc. The final anonymized datasets, created as described above, will be handed over to statistical analysts with simplified case identification.

The analysis will be performed using statistical software (R, SAS, SPSS, or other statistical software) on computers of internal and external research institutes (Kobe University (Kobe, Japan) and deCult Co., Ltd. (Hatsukaichi, Japan)). Data will not be shared, except among computers that process and analyze them.

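### Excluding patients from the whole study for incomplete treatment history or undefined missing data selects on record completeness and may bias overall survival

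*Protocol article*

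**What the plan says.** Table 1 lists as an exclusion criterion "Inadequate data extraction (e.g., missing details on past cancer treatment at other hospitals or individual patient data". The list is open, and neither the required variables nor a threshold is given. Section 2.2 repeats part of the rule: "Patients with unknown treatment history will be also excluded". Just before that, it provides a safeguard: "missing data will be supplemented by a direct check of medical records in cases of inconsistency or lack of information". The abstract names the criterion among the key exclusions.

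The primary endpoint is OS (section 2.3). According to section 2.2, treatment start dates come from the chemotherapy protocol system, and death and last-known-alive dates come from both the record system and the National Cancer Registry.

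The DPC data are described in the Introduction as a source "which is the Japanese claims record for acutely hospitalized patients, including information on the main diagnosis, interventions, and comorbidities". Section 2.2 states that "costs, and history of smoking (Brinkman index) can be extracted from the DPC data", and complications are listed there too. The cohort is wider than inpatients: "Treatment information, including inpatient and outpatient therapies, particularly chemotherapy regimens, can be retrieved from a shared chemotherapy protocol system". Entry requires treatment at a DPC hospital, not an admission.

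Under Strengths and Weaknesses the article says: "The cohort will comprise a certain number of patients who are unable to participate in clinical trials owing to their age". It also claims more realistic data and less loss to follow-up.

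**The concern.** The criterion acts at eligibility, so it governs every analysis, including those that do not use the missing item. A patient treated earlier at another hospital, whose earlier records cannot be obtained, is lost to the OS estimate even when the start date in this hospital group and the vital status are known. No later handling of missing data can bring back a patient who was never in the cohort.

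The study's purpose is to show outcomes in patients as they are actually treated. If survival differs between patients with complete and incomplete records, the reported OS describes only the former. Because the scope of the missing individual data is undefined, each cancer sub-project could also apply the rule differently.

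A second, smaller issue concerns the prognostic models. If smoking and complications are known only for admitted patients, models that include them may be fitted on an admitted subset.

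**Working it through.** **1. The plan's own figure.** The Table 3 rows sum to 800 + 10,000 + 10,000 + 1,000 + 5,000 + 500 + 350 + 500 + 10,000 + 1,500 + 5,000 + 2,500 + 350 + 350 + 1,000 = 48,850, which matches the abstract. No allowance for data-based exclusions is visible.

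**2. What OS needs and where it is held.**
- Start date: chemotherapy protocol system (section 2.2).
- Death or last date known alive: record system and cancer registry (section 2.2).
- Prior treatment elsewhere: not needed to compute survival from the first registered treatment, but needed to assign line of therapy.

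**3. Possible size of the bias.** The article gives no excluded share, no hazard ratio and no median. Assumptions: exponential survival, retained median 12 months (hazard l = ln 2 / 12 per month), excluded share e, and hazard ratio h for excluded versus retained patients.

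All-patient survival: S(t) = (1 − e)·exp(−l·t) + e·exp(−h·l·t).

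At 12 months the retained value is 0.5, so the overstatement is e·(0.5 − 2^(−h)). The all-patient median solves S(t) = 0.5.

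| e | h | all-patient median (months) | overstatement of 12-month OS (points) |
|---|---|---|---|
| 5% | 1.5 | 11.75 | 0.7 |
| 20% | 0.67 | 12.94 | −2.6 |
| 20% | 1.0 | 12.00 | 0 |
| 20% | 1.5 | 11.03 | 2.9 |
| 30% | 0.67 | 13.46 | −3.9 |
| 30% | 2.0 | 9.63 | 7.5 |

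Example: e = 0.20 and h = 1.5 give 0.20 × (0.5 − 0.3536) = 0.029.

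**4. Against sampling error.** The 95% half-width at 50% survival, ignoring censoring, is 1.96·√(0.25/n). This is 0.98 points at n = 10,000 (breast, colorectal and lung) and 5.24 points at n = 350 (kidney, uterine body and uterine cervix). With h = 1.5, the bias passes the half-width when e exceeds 0.0098 / 0.1464 = 6.7% in the large cohorts, and 0.0524 / 0.1464 = 35.8% in the small ones.

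**5. The inpatient variables.** Section 2.2 merges patient, treatment and registry data and describes the exclusions at that stage. Admission, prescription and laboratory data are added afterwards. No passage makes a missing smoking or complication value a ground for exclusion, so the effect is on adjusted models only.

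Section 2.5 foresees models covering different numbers of cases and compares them by AIC or BIC per case. For Cox models this does not remove the dependence on n. With no covariates, no ties and no censoring, the partial likelihood is 1/n!, so −2 log-likelihood per case is about 2(ln n − 1). That is about 16.4 at n = 10,000 and 15.0 at an assumed n = 5,000, a gap of 2 ln 2 = 1.39 that reflects no difference in fit.

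**The case against.** The strongest defence is that prior treatment matters. Without it, the first regimen in this hospital group may not be first-line, and the study wants to compare practice with trial results, where line of therapy counts. That stands for line-specific analyses. It does not justify removal from every analysis.

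Chart review comes first and may shrink the group considerably, and the abstract discloses the exclusion openly. Both stand. Patients whose history stays unknown are still removed, however, and disclosure does not undo selection. Saying that all patients will be identified is also compatible with later exclusions, so there is no formal contradiction.

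A reader might infer that outpatient-only patients are excluded, so that the OS estimate over-represents admitted patients. The documents do not support this: no passage ties exclusion to missing DPC variables, and the order of steps in section 2.2 points the other way. Nor are comorbidity data wholly inpatient, since section 2.2 also lists receipt diagnoses recorded in routine practice.

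How missing covariates are handled may properly be left to an analysis plan. The remark on differing case numbers does not commit the study to complete-case analysis.

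**Conclusion.** The point holds in a limited form. The exclusion is broader than the primary endpoint requires, its scope is undefined, and it may bias OS. The Strengths and Weaknesses section lists many extraction limits but not this one.

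The size is not determinable from the article. Across assumed exclusions of 5–30% and hazard ratios of 0.67–2.0, the error in 12-month OS runs from −3.9 to +7.5 points, and it is zero if excluded and retained patients have the same survival. In the cohorts of 10,000, a moderate effect would exceed sampling error. In those of 350 it mostly would not.

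A reader might conclude that the OS estimate is undermined or too optimistic. Neither is shown, because the excluded share and the survival of those excluded are unknown. The inpatient-data issue is secondary: it bears on the adjusted prognostic models and their comparison, not on crude OS.

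**What to change.** - For OS, limit the data-based exclusion in Table 1 and section 2.2 to patients without a treatment start date or any survival information.
- Keep unknown prior treatment as a category, and exclude it only from line-of-therapy analyses.
- State that missing smoking or complication data do not exclude a patient.
- Report the number, baseline features and OS of patients with incomplete records, show OS with and without them, and name this selection among the limitations.
- Compare AIC and BIC only between models fitted on the same patients.

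The cost is a wording change in Table 1 and sections 2.2 and 2.5, plus some extra analysis. The downside is a heterogeneous group with unknown prior treatment, which will mix lines of therapy. The imputation method, if any, can be left to the analysis plan.

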## Data Availability

Not applicable.
